## 5.2. Test Brace

The test brace results from a combination of semi-automatic generation process and iteration of simulations of the immediate effect of the brace in order to guide the modification of the shape and to improve the topology of the brace before manufacturing.

The test brace will be designed following a new design method. First, a personalized finite element model (FEM) will be created from 3D reconstructions of the patients' spine, pelvis, rib cage and sternum, on which the geometry of the skin is registered and connected by deformable elements simulating the patient's soft tissues. From this basic configuration, the total straightening of the spine in the frontal plane and the alignment of the vertebrae in the transverse plane will be simulated, resulting in a deformed trunk geometry. The surface of the trunk will then be extracted and cut using anatomical landmarks of the skeleton to give the preliminary shape of the brace.

The tightening of the initial brace will then be simulated in the FEM: the geometry of the brace is superimposed on that of the patient and a gradual tightening of the straps is imposed. Contact elements between the surface of the trunk and the inside of the brace transmit the tightening forces of the brace to the patient's model until a position of equilibrium is reached. By extracting the compressive forces acting on the vertebral epiphyseal growth plates out of the brace and into the tight brace the immediate brace correction is simulated.

In order to systematize the design and converge towards an optimal design, the initial brace is modified in an iterative process, using the results of the immediate simulation. Modifications can be made manually (by manually modifying the brace topology) or automatically (by following an optimization process). At each iteration, the brace is simulated by the FEM and its immediate effectiveness is evaluated by an objective function combining the simulated 3D corrections/evolution (immediate and post-growth) and the pressures exerted on the skin.

The optimization automatically iterates different brace designs and evaluates the objective function for each new design. By using global optimization algorithms (substitute optimization, shape recognition, etc.), these changes are guided to converge towards an optimal solution that would maximize the effectiveness of the brace according to the objective function. Several simplifications must be implemented in order to ensure that a solution is reached within a reasonable time. Therefore, at the final stage of the design process, the optimal brace found will be checked and refined manually to ensure its sufficient resolution, smoothness and feasibility of manufacture. The iteration process will be performed by a graduate student in engineering under the supervision of an orthopedic surgeon.

### Proof of concept and preliminary results

The process for generating optimized braces was tested numerically on eight cases by comparing their correction efficiency with that of reference braces. The design time required was five minutes for the semi-automatic process and approximately 1h30 for the reference brace. For these preliminary results, the immediate lumbar correction was significantly better (55% vs 31%,  $p = 0.004$ ) for an equivalent level of pressure exerted on the trunk.

The immediate correction simulation method has already been carried out by our group. It had been shown that the position lying on the back made it possible in part to correct the deformation of the column and that the Providence-type brace came to rebalance the forces on the growth plates of the vertebrae.

The brace will be adapted to include a compliance monitor. This will in no way affect the correcting effect of the brace. The compliance monitor is an iButton thermal sensor ( *Boston Brace, MA, USA* ), this will record the wearing time of the brace. The new type of brace (test brace) will be manufactured in the same way by CAM and thermoforming in the facilities of Orthèse-Prothèse Rive-Sud .

## **6. Methodology**

### **6.1. Study design**

A prospective, double-blind, non-inferiority, controlled and randomized clinical trial will be conducted to assess the effectiveness of a new orthopedic brace design platform. Fifty-eight patients will be recruited at the CHU Ste-Justine orthopedic clinic. The study will be divided into two phases. The first phase will use a crossover design to assess the immediate correction of both types of brace. The second phase will use a parallel design with a 1:1 allocation to assess the mid-term correction.

In phase 1, each patient will try on each type of brace with a “control: test” or “test: control” trial sequence. Immediate correction in braces will be assessed. During phase 2 each patient will use one of the two types of braces for a period of two years. There will be a renewal of the brace after 6 or 12 months based on updated spine x-rays and a new trunk geometry. This is in order to consider the growth of the patient and the inherent changes in the patient's body and the scoliotic deformity. Taking into account that all patients do not follow the same growth, renewal of the brace may sometimes be necessary before 12 months (for example after 6 months following a rapid growth spurt). In this case, the brace will be renewed before the end of 12 months to ensure adequate follow-up of the treatment by the patient. If the patient is part of the test group, the optimization of the correction will be redone.

## 6.2. Recruitment method

All potential subjects presenting to the scoliosis clinics of the CHU Sainte-Justine will be recruited on a voluntary basis, through the clinical research unit in orthopedics (URCO). Potential candidates will be met by the URCO nurse coordinator who will provide them with the study information and consent form, answer questions from the patient and/or parents, and direct them to the orthopedist after agreed to join the study and signed the consent form. The characteristics and motivations of the subjects refusing to take part in the study will be kept in order to verify the presence of a selection bias in the sample if this number turns out to be significant. According to our previous experience , the vast majority of subjects agree to participate in this type of study.

## 6.3. Inclusion and exclusion criteria

**Inclusion criteria:** Patients (girls or boys) must have received a confirmed diagnosis of adolescent idiopathic scoliosis (thus aged between 10 and 16 years inclusive ) regardless of the type of curve (I to VI) according to the Lenke classification . All subjects will be candidates for brace treatment according to the criteria recommended by the Scoliosis Research Society  : thoracic/lumbar/thoracolumbar scoliosis between 20 ° and 40 °, as measured by the Cobb technique on a PA radiograph; a Risser index between 0 and II (before skeletal maturity); <18 months after menarche .

**Exclusion criteria:** Will be excluded from the study, subjects with a history of cardiovascular disease, neurological disorders, including myopathy, neuropathy or disorders of the central nervous system, or any other disease of the musculoskeletal system at the level of the legs. Patients with spondylolisthesis of grade greater than 1 will be excluded from the study. Patients with pregnancy will also be excluded from the study.

The use of these standard criteria for the indication of brace treatment in this randomized controlled clinical trial ensures that we have generalizable results and constitutes an ethical approach since this study concerns the majority of the population of patients eligible for brace treatment.

## 6.4. Method and follow-up visits

### **Visit 1: Acquisition of parameters**

During the initial visit, the following interventions will be performed :

- An EOS low-dose digital biplanar radiograph (EOS-Imaging, Paris, France) will be acquired: simultaneous AP and lateral while the patient is standing in a comfortable position, with hips and knees extended, both elbows bent with the hands at the side of the head. A student will digitize the anatomical landmarks on each x-ray, so as to obtain a 3D reconstruction of the spine, pelvis and rib cage. A scanning technician, blind to the purposes of our study and the subject's allocation group, will verify and approve each of the reconstructions. The relevant geometric variables will be obtained automatically on

Clindexia, eliminating any possibility of radiological measurement bias by a human observer.

- Curve flexibility will be qualitatively assessed by the orthopedist to determine if the patient has a flexible, normal, or rigid curve
- A scan of the external surface of the trunk will be acquired with the TechMed3D surface scanner.
- The SRS-22r questionnaire will be administered. This questionnaire is administered to patients in the scoliosis clinics at the CHU Sainte-Justine even if they are not part of a research project at all visits (except for the delivery of a brace). The questionnaire is administered through the AMIKO platform (platform developed by the CHU Sainte-Justine to computerize the questionnaires at the orthopedic clinic), or the questionnaire is administered in paper version.

### **Design and manufacture of braces**

Before the second visit, which will take place approximately one month after the first, each patient will have a control brace and a test brace designed and manufactured according to the specific geometry of their trunk and spine as described in Section 5.

### **Visit 2: Cross-testing of the braces and delivery of the brace in the medium term**

During Visit 2, each patient will sequentially try on both braces. This corresponds to phase #1 (crossover design) of the study mentioned in section 6.1. The following interventions will be made:

The first brace will be delivered, and the location of the corrective supports, the overall conformation of the brace and the tension of the straps will be checked by the orthotist for the control brace and for the test brace. Neither the orthopedist nor the orthotist can modify the corrective effect of the test brace in their adjustments. The same manipulations will then be repeated with the second brace in the randomization sequence.

A digital x-ray will be taken in a supine position with the patient in a comfortable position, with the hips and knees extended, the hands in a lateral position relative to the head. The Cobb angle will be measured by an evaluator blind to the aims of the study. The same manipulations will then be repeated with the second brace in the randomization sequence.

- The patient will receive the brace corresponding to the group assigned to him by the randomization for phase #2. He will also receive the usual instructions for wearing the brace, unless he meets a failure criterion (see section 6.5).

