
correction generated by the brace and its long-term effect, ie its ability to prevent the progression of scoliotic deformities, has been demonstrated from a biomechanical point of view. A strong correlation between the immediate correction of the Cobb angle of the frontal curves and the correction of the asymmetry of the pressures on the growth plates has been found .

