## 4. Objective and assumptions

**The general objective** of the project is to validate the new CAD/CAM brace design method integrating the optimization of immediate correction.

**Primary Hypothesis (H1)** : After 1 year and 2 years of use, the out-of-brace correction, as measured by Cobb's angle, from the Test braces will be non-inferior to the Control braces. The non-inferiority margin will be 5 degrees.

**Secondary hypothesis (H2)** : The immediate and medium-term (1 and 2 years) failure rate of treatment will be 10% lower for Test braces compared to Control braces. There are three different types of failures:

1. Mid-term failure (1 and 2 years) – relative progression : A progression of the out-of-brace Cobb angle of 5 degrees or greater than the value measured at visit 1.
2. Intermediate (study duration) failure – absolute progression : A progression of the Cobb angle of the main off-brace curvature to greater than 45 degrees (SRS failure criterion).
3. Medium-term failure (duration of the study) – surgery : Stopping treatment with a brace and a decision to have surgery (AVBGT or fusion).

**Secondary hypothesis (H3)** : The quality of life of patients wearing Test braces in the medium term, as measured with the SRS-22r questionnaire, will be non-inferior to that of patients wearing control braces. The non-inferiority margin will be 10%.

**Secondary hypothesis (H4)** : The immediate in-brace correction of the Cobb angle of the Test brace will be no less than that of the control brace. The non-inferiority margin will be 5 degrees.

The effects measured (dependent variables) are as follows:

| Effects measures                                                         | Descriptions                                                                           |
|--------------------------------------------------------------------------|----------------------------------------------------------------------------------------|
| Major                                                             |                                                                                        |
| Cobb angle off brace (Initial, 6 months, 1 year, 2 years).               | Measure using low-dose EOS radiography to assess the evolution of scoliosis.           |
| Secondary                                                         |                                                                                        |

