## **7. Randomization**

Patients who meet all the inclusion criteria and no exclusion criteria will be randomized twice independently.

Randomization #1 will be to determine the trial sequence of brace types at Visit #2. Randomization #1 allocation will have a 1:1 ratio for the “test:control” sequence and the “control” sequence. : test ”.

Randomization #2 will be to determine the brace type the patient will use for a period of two years after the visit. The allocation will have a ratio of 1:1 for test and control brace type respectively.

The randomization will be done by the URCO nurse coordinator according to a block allocation of 2, 4 or 6. Neither the engineers nor the orthopedist nor the orthotist will know the brace assigned for phase #2 until these are designed, manufactured and adjusted.

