## 8. Statistical analysis plan

### 8.1. Sample size justification

The sample size was calculated to be able to accept the main hypothesis (H1) with a probability of 5% of committing the type I error and a power of 80%. The calculation was performed with nQuery software (GraphPad Software DBA Statistical Solution, San Diego, CA) and the following parameters were used:

- Significance level  $\alpha = 5\%$
- Allocation ratio  $k = 1$
- Margin of non-inferiority  $\delta = 5^\circ$
- standard deviation  $\sigma = 7^\circ$ 
- Power  $(1 - \beta) = 80\%$

The sample size should be 25 per group, so a total of 50 patients. On the other hand, a loss to follow-up of 15% is anticipated. We will therefore need 29 patients per group for a total of 58 patients.

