### 8.3. Analysis of primary hypothesis H1

The analysis of primary hypothesis H1 will have the off-brace Cobb angle as the dependent variable and the type of brace worn as the independent variable. The 95% confidence interval of the difference in correction between the test brace and the control brace will be constructed and compared to the non-inferiority margin.

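### The H1 analysis names no covariate, although Visit 2 gives every patient an in-brace Cobb angle in both braces; the unadjusted comparison is valid but may give up precision.

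*Protocol*

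**What the plan says.** - **Data collected.** Protocol section 6.4, Visit 2: "During Visit 2, each patient will sequentially try on both braces". A supine in-brace x-ray is taken with each brace and the Cobb angle is measured. The patient then receives the phase 2 brace.
- **Rationale.** Section 3.3 describes a link, shown biomechanically, between immediate correction and the prevention of progression. It reports "A strong correlation between the immediate correction of the Cobb angle of the frontal curves and the correction of the asymmetry of the pressures". The pressures meant are those acting at the vertebral growth plates, and no coefficient is given.
- **H1 analysis.** Section 8.3 takes the off-brace Cobb angle as outcome and "the type of brace worn as the independent variable". It then states: "The 95% confidence interval of the difference in correction between the test brace and the control brace will be constructed". This interval is set against the margin. No covariate is named.
- **Other uses of the Visit 2 angles.** They are the outcome for H4 (section 8.6). They also enter the rule under which a patient may be moved to the other group's brace (section 6.5).
- **Concealment.** Section 7: "Neither the engineers nor the orthopedist nor the orthotist will know the brace assigned for phase #2 until these are designed, manufactured and adjusted".

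**The concern.** The crossover phase gives both arms the same two measurements per patient, taken before the assigned brace is worn. They carry information on how far a curve can be corrected, which the Visit 1 standing angle alone does not show. If that is related to the later off-brace angle, leaving it out of the H1 model leaves explainable variation in the error term.

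The trial has little room to spare. With 25 evaluable patients per group, the unadjusted two-sided 95% half-width is 3.98 degrees against a margin of 5, so the estimate may favour the control brace by only about 1.02 degrees before non-inferiority is missed. If r were 0.5, chance imbalance in correctability would by itself contribute a standard deviation of 0.5 × 7 × sqrt(2/25) = 0.99 degrees to the H1 difference. The unadjusted interval already allows for this. What is at stake is the width of the interval, not bias.

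**Working it through.** **Inputs.** Margin: "The non-inferiority margin will be 5 degrees" (section 4). SD 7 degrees, 1:1 allocation, 25 evaluable per group (section 8.1). True difference 0 (assumed, not stated). r is the partial correlation of the mean Visit 2 in-brace angle with the 1- or 2-year off-brace angle, beyond the other model terms. The protocol does not give r, so a range is shown.

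**Step 1: the plan's own figure.** Section 8.1 sizes the trial "with a probability of 5% of committing the type I error and a power of 80" per cent, with no sidedness stated.
- One-sided 5%: n = 2 × 7² × (1.645 + 0.842)² / 5² = 24.2, so 25 per group. This matches. The non-central t distribution gives 80.1% power at 25.
- One-sided 2.5%, which is what a two-sided 95% interval implies: 2 × 7² × (1.960 + 0.842)² / 5² = 30.8, so 31 per group (32 by the t distribution). At 25 per group, power is 70%.

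**Step 2: effect of adjustment.** Residual SD s = 7 × sqrt(1 − r²). Half-width = t(0.975, df) × s × sqrt(2/25), with df 48 unadjusted and 47 with one covariate. Power is the probability that a non-central t variable with non-centrality 5 / (s × sqrt(2/25)) exceeds the critical value.

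| r | s | 95% half-width | Power, two-sided 95% CI | Power, one-sided 5% |
|---|---|---|---|---|
| 0 (unadjusted) | 7.00 | 3.98 | 70% | 80% |
| 0.2 | 6.86 | 3.90 | 71% | 81.5% |
| 0.3 | 6.68 | 3.80 | 74% | 83% |
| 0.5 | 6.06 | 3.45 | 81.5% | 89% |

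Example, r = 0.5: 2.012 × 6.06 × sqrt(2/25) = 3.45. Charging a second degree of freedom, for the Visit 1 angle, changes the half-widths by about 0.002 degrees and power by less than 0.1 percentage point. The table ignores the small loss from chance imbalance in the covariate itself, so for r near 0 the net gain may be nil or slightly negative.

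**Step 3: which form of the covariate is safe.** A simulation used 5,000 repeats, 25 per group, an in-brace result 2 degrees better with the test brace, and an outcome driven by the correction in the brace worn (assumed correlation 0.5). The true effect was 1.57 degrees.
- Unadjusted: mean estimate 1.55, standard error 2.02.
- Adjusted for the mean over both braces: 1.55, standard error 1.78.
- Adjusted for the value in the assigned brace only: −0.02.

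The mean of both braces leaves the effect intact and reduces the standard error. The assigned-brace value lies on the causal path and removes the effect that H1 is meant to estimate.

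**The case against.** The strongest reply is that nothing here is an error. A randomised unadjusted comparison is valid, and covariates are often settled in a separate statistical analysis plan, which is not at hand. This stands in part: the point concerns efficiency, not validity. However, section 8.3 belongs to the protocol's own statistical analysis plan and names one explanatory variable, so it is the place to add the covariate.

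Four stronger readings are tempting, and the protocol does not support them.
- *That the protocol says in-brace correction predicts the two-year result.* Section 3.3 speaks of a biomechanical link, and the correlation it reports is with growth-plate pressure asymmetry. No correlation with the 1- or 2-year off-brace angle is given.
- *That the phase 1 data are discarded.* They serve H4 and the reassignment rule in section 6.5. Only the H1 model omits them.
- *That omitting the covariate causes the 70% power.* That figure comes from testing a sample sized at one-sided 5% with a two-sided 95% interval, which is a separate matter. On the section 8.1 basis the unadjusted power is 80%.
- *That concealment at the time of measurement is already secured.* Section 7 protects the allocation only until the braces are adjusted, and section 6.4 places the fitting check before the x-ray. The evaluator is described as blind to the aims of the study; allocation is not mentioned there.

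Two technical objections also have force. A correction score formed as the standing Visit 1 angle minus the supine in-brace angle mixes posture and imaging system with brace effect, and contains the baseline value. Entering the in-brace mean and the Visit 1 angle as separate terms deals with the overlap. The posture difference applies to both arms alike and may lower r. In addition, Visit 1 already includes a qualitative flexibility grade, which may capture part of the same information.

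**Conclusion.** The point holds as a recommendation to improve precision. Section 8.3 names no covariate for H1, while the design supplies a pre-wear measurement, defined identically in both arms, that the protocol itself considers relevant on biomechanical grounds. The unadjusted analysis is not wrong.

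The size of the gain is unknown because r is unknown. At r = 0.2 it is negligible (0.08 degrees of half-width, about 1 percentage point of power). At r = 0.3 it is modest (0.18 degrees, 3 to 4 points). At r = 0.5 it is material (0.53 degrees, 9 to 12 points). The direction is the same on either reading of sidedness. These figures assume SD 7, a true difference of 0 and 25 evaluable patients per group. The protocol does not say whether SD 7 refers to the final angle or to change from baseline; if it is change, r must be read as the correlation remaining after baseline is accounted for.

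**What to change.** 1. In section 8.3, prespecify an H1 model with brace group, the Visit 1 off-brace Cobb angle, and the mean of the two Visit 2 in-brace Cobb angles. Define the mean identically in both arms, and state that the in-brace value for the assigned brace alone will not be used as a covariate.
2. In section 7, state that the phase 2 allocation stays concealed until both in-brace x-rays have been taken and measured.
3. State how patients without Visit 2 data are kept in the intention-to-treat analysis, for example by imputing the covariate with the overall mean, calculated without regard to arm.

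The cost is a few sentences, one degree of freedom per covariate and a simple imputation rule. No extra visits, x-rays or patients are needed. The covariate should be fixed before outcome data are seen.
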